# Effectiveness and cost-effectiveness of rehabilitation after lumbar disc surgery (REALISE): design of a randomised controlled trial

**DOI:** 10.1186/1471-2474-14-124

**Published:** 2013-04-05

**Keywords:** Rehabilitation, Exercise, Physiotherapy, Lumbar disc surgery, Lumbar disc herniation, Randomised controlled trial, Economic evaluation

## Abstract

**Background:**

Patients who undergo lumbar disc surgery for herniated discs, are advocated two different postoperative management strategies: a watchful waiting policy, or referral for rehabilitation immediately after discharge from the hospital. A direct comparison of the effectiveness and cost-effectiveness of these two strategies is lacking.

**Methods/Design:**

A randomised controlled trial will be conducted with an economic evaluation alongside to assess the (cost-) effectiveness of rehabilitation after lumbar disc surgery. Two hundred patients aged 18–70 years with a clear indication for lumbar disc surgery of a single level herniated disc will be recruited and randomly assigned to either a watchful waiting policy for first six weeks or exercise therapy starting immediately after discharge from the hospital. Exercise therapy will focus on resumption of activities of daily living and return to work. Therapists will tailor the intervention to the individual patient’s needs. All patients will be followed up by the neurosurgeon six weeks postoperatively. Main outcome measures are: functional status, pain intensity and global perceived recovery. Questionnaires will be completed preoperatively and at 3, 6, 9, 12 and 26 weeks after surgery. Data will be analysed according to the intention-to-treat principle, using a linear mixed model for continuous outcomes and a generalised mixed model for dichotomous outcomes. The economic evaluation will be performed from a societal perspective.

**Discussion:**

The results of this trial may lead to a more consistent postoperative strategy for patients who will undergo lumbar disc surgery.

**Trial registration:**

Netherlands Trial Register:
NTR3156

## Background

The lumbosacral radicular syndrome, also called sciatica, is commonly caused by a herniated disc
[1]. The syndrome is z=s: characterised by lower limb pain radiating below the knee in an area of the leg served by one or more lumbosacral nerve roots. Sometimes there are neurological phenomena such as sensory and motor deficits. In the Netherlands, the incidence of sciatica increased from 75,000 to 85,000 cases per year over the past decade
[2,3]. The direct and indirect costs of patients suffering from sciatica approximate 1.2 billion Euros per year
[2]. The natural course of sciatica is favourable in the majority of patients
[4]. The international consensus is that surgical treatment is offered if the radiating leg pain persists despite a period of conservative management
[5]. It is estimated that about 12,000 operations for herniated lumbar discs are performed in the Netherlands each year
[3]. Rates of spinal surgery differ across countries and within one country
[6]. Rates in the United States are 30% higher than in the Netherlands, 50–60% higher than in Canada and 80% higher than in the UK
[7].

In the long term, surgical and non-surgical management are equally successful
[8,9]. Recovery rates between 78 and 95% were found 1–2 years postoperatively
[8-13] However, shortly after surgery results vary, with recovery rates of 46–75% 6–8 weeks postoperatively
[8,9,13] This variation may be due to differences in defining recovery, but also due to different referral patterns for rehabilitation. It implies a poor outcome in up to 54% of the patients at short term follow up, and up to 22% of the patients at ≥ 1 year follow up. As this group of patients highly contributes to the direct and indirect costs of lumbar disc surgery, an important aim of postoperative treatment is to prevent the development of chronic symptoms
[14].

Currently, postoperative care and management, including referral for rehabilitation (i.e. exercise therapy and advice provided by physiotherapists or exercise therapists), varies between hospitals and surgeons. A national survey in the Netherlands amongst spinal surgeons (both neurosurgeons and orthopaedic surgeons) showed that 65% of the surgeons always refer patients for postoperative physiotherapy after discharge, whereas 24% never refer patients for postoperative physiotherapy and 11% sometimes. Likewise, 45% of the surgeons consider physiotherapy after discharge to be essential, but 30% of the surgeons strongly disagree that physiotherapy would be essential
[15]. A similar trend was seen in a national survey in the UK where 55% of the surgeons did not send their patients for physiotherapy following spinal surgery
[16]. In another UK survey physiotherapists providing care to patients who had undergone lumbar disc surgery reported a wide variety of treatment contents being delivered. Moreover, this study revealed considerable variation in access to postoperative physiotherapy for outpatients
[17].

Patients are usually referred for rehabilitation during hospitalisation
[15]. The two most common options for management after discharge are continued rehabilitation or a watchful waiting policy. The first option consists of continued rehabilitation offered to all patients. The second option comprises watchful waiting during the first weeks advising to return to an active lifestyle, with postoperative treatment only for those patients having persisting symptoms after six to eight weeks. Several randomised controlled trials investigated the effectiveness of rehabilitation following primary lumbar disc surgery
[18]. For exercise programmes starting 4–6 weeks postoperatively, there is moderate evidence that they are more effective in improving physical function, and low quality evidence that they are more effective than no treatment in decreasing pain. There is moderate evidence that high intensity exercises are more effective in improving physical function compared to low intensity exercises, and low quality evidence that they are more effective in decreasing pain. However, high quality studies assessing the effectiveness of immediate postoperative interventions are lacking
[18]. Besides, data on cost-effectiveness of postoperative management is scarce
[19]. Therefore, the aim of the Rehabilitation After Lumbar Disc Surgery (REALISE) study is to evaluate the effectiveness of an exercise therapy intervention starting in the first postoperative week, compared to a watchful waiting policy during the first 6–8 weeks after surgery. Furthermore, cost-effectiveness will be assessed by means of an economic evaluation from a societal perspective.

## Methods/Design

### Design

A multicentre randomised controlled trial will be conducted, together with a full economic evaluation.

### Setting

Participants will be recruited from 10 hospitals, both urban and regional, in three regions in the Netherlands, where lumbar disc surgery is performed. Primary care physiotherapists and exercise therapists in the catchment areas of these hospitals will provide rehabilitation following this lumbar disc surgery. Prior to the start of the trial all participating therapists will follow a training session in which both the study design and treatment protocol for the intervention group will be explained.

### Ethical approval

The Medical Ethics Review Board of the VU University Medical Centre approved the study protocol in September 2011 (registration number NL35897.029.11). Subsequently, local review boards of each participating hospital approved the protocol.

### Participants

Patients will be eligible for inclusion if they meet all of the following inclusion criteria:

lumbar disc herniation confirmed by MRI and physical signs of nerve root compression corresponding to the level of disc herniation,

between 18 and 70 years of age,

able to fill out Dutch questionnaires themselves,

and provide written informed consent.

Patients will be excluded if they meet any of the following criteria:

cauda equina syndrome,

neurogenic claudication,

co-morbidities of the lumbar spine (e.g., fractures, carcinomas, osteoporosis),

prior spinal surgery in the last 12 months,

previous lumbar disc surgery at the same level and same side,

pregnancy,

or contra-indications for exercise therapy (e.g., acute respiratory or cardiovascular complaints, acute systemic infections).

### Participant recruitment

Figure 
1 comprises the flow diagram of the REALISE trial. Neurosurgeons will inform all patients with a clear indication for lumbar disc surgery about the study and will refer potentially eligible participants to the research team prior to surgery. The neurosurgeon will register whether the patient would normally have been referred for postoperative rehabilitation or not. A research nurse will subsequently invite the patients for an intake preceding surgery and then check eligibility criteria and provide details about the trial procedures. If the patient consents to participate, baseline measurements will be administered.

**Figure 1 F1:**
[figure not shown]
Flow diagram of the REALISE trial.

### Treatment allocation

To conceal treatment allocation, randomisation lists per hospital will be generated by computer prior to study commencement by an independent person. To achieve the predetermined size of treatment and control group, weighted block randomisation (blocks of four) will be used. Directly after having received the completed baseline questionnaire, the research nurse will open the next consecutive a priori prepared numbered opaque envelope containing the assigned postoperative strategy. Patients allocated to the intervention group will receive a list of the participating therapists and are asked to make an appointment for the first treatment session in the first week after surgery. Within one week post-surgery the research nurse will contact the patient to ensure that an appointment has been made and to record the date of the first appointment.

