### Blinding

Neurosurgeons will be blinded for group allocation, as randomisation and group allocation is performed after their involvement in participant recruitment. The research nurses will inform participants on treatment allocation and can, therefore, not be blinded. The nature of the postoperative strategies precludes blinding of the patient and the therapist. Besides, all measures are patient reported outcomes, and therefore outcome assessment is not blinded. The unequal size of intervention and control group, necessary for multilevel analysis, prevents blinding of the researcher and the statistician involved in outcome analyses.

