### Sample size

Power calculations were based on a Cochrane review assessing the effectiveness of rehabilitation following lumbar disc surgery
[18] and were performed for the three main outcomes (for all: power 0.9; alpha 0.05). To detect a clinical relevant mean difference in a multi-level analysis between the continued rehabilitation group and the watchful waiting group of 8 points on the ODI (SD 15), a total of 165 patients is needed. To detect a difference of 2 points (SD 3) for pain (11-point NRS) a total of 105 patients is needed. For detecting a 20% difference on the dichotomised global perceived recovery (recovered vs not recovered) a total of 150 patients is needed. Anticipating 15% potential study withdrawal, a total of 200 patients will be recruited. Participants will be unequally distributed (109 intervention vs. 91 control) to allow for multilevel analysis, taking into account the multilevel structure of the data in the intervention group.

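### One fixed block size of four on each hospital's list, with an unblinded nurse role that both screens patients and opens the envelopes, leaves part of the allocation sequence predictable

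*Protocol article*

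**What the plan says.** Under Treatment allocation, "randomisation lists per hospital will be generated by computer prior to study commencement by an independent person", and "weighted block randomisation (blocks of four) will be used". Four is the only block size named. Once the completed baseline questionnaire has been received, "the research nurse will open the next consecutive a priori prepared numbered opaque envelope containing the assigned postoperative strategy".

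Under Participant recruitment, after referral by the neurosurgeon, "A research nurse will subsequently invite the patients for an intake preceding surgery and then check eligibility criteria and provide details about the trial procedures". The Blinding section adds: "The research nurses will inform participants on treatment allocation and can, therefore, not be blinded". It also says that patients and therapists cannot be blinded and that all measures are patient-reported.

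Under Sample size, "Participants will be unequally distributed (109 intervention vs. 91 control) to allow for multilevel analysis". Under Setting, "Participants will be recruited from 10 hospitals, both urban and regional".

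The article does not give the composition of the blocks. Nor does it say whether nurses know the block size, who takes consent, who keeps the envelopes, or whether one individual performs all the nurse's steps at a hospital.

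**The concern.** A sealed opaque envelope stops anyone reading the next allocation. It does not stop someone working it out from those already opened. Three stated features make that possible here: the list is short and local to one hospital, the block size is small and constant, and the role that opens the envelopes also deals with patients before they enter.

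If a nurse has a good idea which arm comes next, that can affect, even without intent, who is pursued for an intake, how a borderline criterion is judged, or how the trial is described. The article's Background reports that surgeons are divided on the value of postoperative physiotherapy, so views about which patients need it are plausible. Selection on motivation or expected recovery would feed directly into self-reported primary outcomes. The adjustment described under Data analysis can correct only for characteristics that were measured.

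**Working it through.** **Inputs.** Block size 4 and separate hospital lists (Treatment allocation); 109 intervention (I) and 91 control (C), total 200 (Sample size); 10 hospitals (Setting), so about 200/10 = 20 patients, or five blocks, per list if recruitment is even (assumption).

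**Reproducing 109:91.** No single composition of four does it: all 2:2 gives 100:100 and all 3:1 gives 150:50. With x blocks of 2:2 and y blocks of 3:1, all complete, 2x + 3y = 109 and 2x + y = 91. Hence y = 9 and x = 41, which is 50 blocks. The share of 3:1 blocks is 9/50 = 0.18. Restricting to these two compositions, and to complete blocks, is an assumption. Below, each block is treated as 3:1 with probability 0.18.

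**Nurse knows size and composition.** In a block with a and b places, the expected number of allocations fixed by earlier ones is a/(b+1) + b/(a+1).
- 2:2: 2/3 + 2/3 = 1.333, and 1.333/4 = 33.3%
- 3:1: 3/2 + 1/4 = 1.75, and 1.75/4 = 43.8%
- Mix: 0.82 × 33.3% + 0.18 × 43.8% = 35.2%, about 70 of 200

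**Nurse knows the size but not the composition.**
- Third place certain only after CC: 0.82 × 1/6 = 0.137.
- Fourth place certain after two C and one I (0.82 × 1/2 = 0.410) or after III (0.18 × 1/4 = 0.045): total 0.455.
- Certain overall: (0.137 + 0.455)/4 = 14.8%, about 30 of 200.

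**Best-guess accuracy, composition unknown.**

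| Place | Probability that the best guess is right |
|---|---|
| 1 | 0.82 × 0.5 + 0.18 × 0.75 = 0.545 |
| 2 | 2 × (0.82 × 1/3 + 0.18 × 1/4) = 0.637 |
| 3 | 0.137 + 3 × (0.82 × 1/6 + 0.18 × 1/4) = 0.682 |
| 4 | 0.455 + 0.410 = 0.865 |

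The mean is 68.2%. Always guessing intervention would be right 54.5% of the time.

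**Predictable with probability at least 0.75, composition unknown.** Add to the certain cases the third place after II (occurs in 0.227 of blocks; C follows with probability 0.182/0.227 = 0.80) and the fourth place after two I and one C (occurs in 0.545; C follows with probability 0.410/0.545 = 0.752). Then (0.137 + 0.455 + 0.227 + 0.545)/4 = 34.1%, about 68 of 200. The last group only just passes the threshold.

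**Nurse does not know the block size.** No allocation is formally certain.

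**Effect of varying the block size.** Take sizes 4, 6 and 8 as equally likely. Let each block be balanced with probability 0.73, or carry one extra intervention place (3:1, 4:2, 5:3) with probability 0.27. The mean block size is 6, so the intervention share is (3 + 0.27)/6 = 0.545, as planned. Simulating 20 patients per hospital, with a nurse who knows this scheme but not the current block, gives about 1% of allocations certain and a best guess right about 63% of the time.

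**The case against.** The list is computer-generated by someone independent, the envelopes are opaque, numbered and prepared in advance, and each is opened only once baseline data are in. Neurosurgeons refer patients before the nurse is involved and are stated to be blinded. Most eligibility criteria are matters of fact, such as imaging, age, earlier surgery and pregnancy. Baseline takes place days to hours before surgery, which leaves little room to hold a patient back for a preferred envelope. Baseline differences will be examined and may be adjusted for. An article also commonly leaves envelope custody and what nurses are told to the full protocol.

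Most of this stands, and it limits the likely harm. It does not remove the problem. None of these safeguards prevents inference from past allocations, and inviting patients, judging eligibility and explaining the trial are stated tasks of the unblinded role.

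A reader might go further and infer that at least a third of allocations are known, that two or three allocations fix the rest of a block, or that concealment is lost. The documents do not support this. One third is the value for all-2:2 blocks, which cannot give 109:91. Under the assumed mix with composition unknown, the last place is still open in 54.5% of blocks, and the next envelope is always sealed. That the nurse takes consent, keeps the envelopes, or is the same individual throughout is also inference. The point needs none of it.

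**Conclusion.** The point holds in limited form. A single block size of four within each hospital, combined with an unblinded role that screens patients and opens envelopes, makes a material minority of allocations predictable. The range is from none formally certain (block size unknown to the nurse), through about 15% (size known, composition not), to about 35% (both known). In the middle case the best guess is right about 68% of the time, against 54.5% for a constant guess.

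These figures rest on the assumed 41/9 mix of complete blocks and on a nurse who can follow every earlier allocation at the hospital. The block size is printed in a public article, but nothing shows that the nurses were told it or acted on it. This is an avoidable weakness in concealment, not evidence of selection bias. It is worth correcting because the correction is cheap and any resulting bias could not be fully repaired in the analysis.

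**What to change.** For allocations still to be made, have the same independent person generate new hospital lists with randomly varying block sizes, for example 4, 6 and 8, and with compositions weighted so that the arms come out at about 109:91. Keep both sizes and compositions out of anything the research nurses receive. Record the scheme, including how the weighting is achieved, in a document held by the list-maker. Keep the envelopes and the requirement for a completed baseline questionnaire as they are.

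The gain is mainly in certainty: with composition unknown to the nurse, from about 15% of allocations certain to about 1%. Best-guess accuracy falls less, from about 68% to about 63%, which is why withholding the details matters as well.

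The cost is a new set of lists and envelopes, slightly larger possible imbalance within a hospital, and final arm sizes that may differ slightly from 109:91. No patient procedure, assessment or analysis changes.

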### Intervention

During hospitalisation all participants, regardless of treatment allocation, will receive usual hospital care. This treatment, provided by a physiotherapist or nurse, mainly consists of providing advice and instructions for transfers and performing activities of daily living, in preparation for discharge. At discharge patients will receive a booklet providing advice and suggestions for exercises. These booklets are part of usual inpatient care and are provided by the participating hospitals.

#### Intervention group: continued rehabilitation

Participants in the intervention group will receive a referral for post-surgery exercise therapy in primary care starting the first week after discharge. During a six to eight week period, participants will receive one or two exercise therapy sessions per week, conform a treatment protocol designed for this trial including information and advice about rehabilitation. The six to eight week period reflects the period before patients consult their neurosurgeon again after the surgery. The exact duration of this period depends on the organisation in the participating hospital in which the patient was operated. The protocol is based on existing protocols for primary care exercise therapy, which were derived from a national clinical guideline
[20]. The main goal is to gradually extend activities of daily living from personal care to housekeeping tasks in the short term and return to work and prepare for sports and leisure activities in the long term. In the first week, therapists will perform physical examinations and focus treatment on the ability and possibility to execute personal care activities and perform transfers (e.g., bed to stand, chair to stand) in the home situation. From the second week onward, exercises will be taught with gradually increasing intensity targeting limitations that were found in the initial postoperative assessment. The exact type of exercises is left to the therapists’ discretion, based on the outcomes of the physical examination and taking patients’ preferences into account. Therapists will provide tailored advice on lifestyle and the execution of activities of daily living. Exercises will aim to prepare for and support the resumption of daily activities. Treatment can be terminated before the end of the six to eight week period if the patient is fully recovered.

Per treatment session, participating therapists will fill out a registration form including amongst others, treatment goals on both a global and more specific level, whether homework was prescribed or not and, if applicable, the reason for terminating the treatment.

#### Control group: watchful waiting policy

Participants assigned to the control group will not receive exercise therapy immediately after discharge from hospital. Patients may consult their neurosurgeon or general practitioner in case of recurring or increasing complaints, but no exercise therapy or other allied health care intervention will be initiated. The research nurses will limit the extent to which they will provide advice in case they will be called by patients allocated to the control group. To prevent diminishing contrast between groups, only advice that has been given during the clinical phase will be repeated.

#### Follow-up consult neurosurgeon

Six to eight weeks after discharge a follow-up consult with the neurosurgeon will take place. Whether patients are referred for further treatment after this follow up consultation is left to the neurosurgeons’ discretion. We will measure all health care consumption using cost questionnaires (see section on Economic evaluation below).

